## Abstract

**Background:**

HIV testing and knowledge of status are starting points for HIV treatment and prevention interventions. Among female sex workers (FSWs), HIV testing and status knowledge remain far from universal. HIV self-testing (HIVST) is an alternative to existing testing services for FSWs, but little evidence exists how it can be effectively and safely implemented. Here, we describe the rationale and design of a cluster randomised trial designed to inform implementation and scale-up of HIVST programmes for FSWs in Zambia.

**Methods:**

The Zambian Peer Educators for HIV Self-Testing (ZEST) study is a 3-arm cluster randomised trial taking place in 3 towns in Zambia. Participants (N=900) are eligible if they are women who have exchanged sex for money or goods in the previous 1 month, are HIV negative or status unknown, have not tested for HIV in the previous 3 months, and are at least 18 years old. Participants are recruited by peer educators working in their communities. Participants are randomised to 1 of 3 arms: (1) direct distribution (in which they receive an HIVST from the peer educator directly); (2) fixed distribution (in which they receive a coupon with which to collect the HIVST from a drug store or health post) or (3) standard of care (referral to existing HIV testing services only, without any offer of HIVST). Participants are followed at 1 and 4 months following distribution of the first HIVST. The primary end point is HIV testing in the past month measured at the 1-month and 4-month visits.

**Ethics and dissemination:**

This study was approved by the Institutional Review Boards at the Harvard T.H. Chan School of Public Health in Boston, USA and ERES Converge in Lusaka, Zambia. The findings of this trial will be presented at local, regional and international meetings and submitted to peer-reviewed journals for publication.

**Trial registration number:**

Pre-results; NCT02827240.

Strengths and limitations of this studyThis study will be one of the first reporting the effectiveness and safety of an HIV self-testing (HIVST) intervention among female sex workers (FSWs).The results will allow for assessment of the feasibility and acceptability of HIV self-test kits in general.The results will provide evidence on whether HIVST is used by FSWs if it is accessible via existing distribution points within the health system.Limitations of this study include the self-reported nature of many of the outcomes, which may lead to social desirability biases.To overcome social desirability biases in the reporting of outcomes, in particular the use of HIVST and HIV status knowledge, we use several innovative measurement approaches.

## Introduction

Female sex workers (FSWs), defined as women who exchange sex for money or goods, bear a disproportionate burden of the HIV epidemic globally.^1^
^2^ Global HIV prevalence among FSWs has been estimated at nearly 12%, with HIV prevalence rising to more than 30% for FSWs living in countries with medium and high background HIV epidemics.^1^ In sub-Saharan Africa in 2011, an estimated 17.8% of all infections in women were attributed to engagement in sex work.^3^ Vulnerability to HIV among FSWs occurs at multiple levels,^4^ which potentiates the HIV epidemic in this population.^2^
^5^ Determinants of HIV among FSWs occur at the individual level (behavioural and biological factors, such as sexually transmitted infections), dyad and partner level (such as power dynamics within relationships), work environment level (organisational structures where individuals work, including venue policies and availability of condoms in venues),^6^ and community and macrostructural levels (including community structure and organisation and legal and policy environments).^2^

In 2014, the Joint United Nations Programme on HIV and AIDS (UNAIDS) put forth a new global target for controlling and ultimately ending the HIV epidemic.^7^ The 90-90-90 target is a three-part target that aims to have 90% of people living with HIV aware of their status, 90% of those diagnosed on treatment and 90% of those on treatment virally suppressed by the year 2020, ultimately resulting in viral suppression for 73% of HIV-infected individuals worldwide. Such a strategy requires regular HIV testing for individuals who are at ongoing risk of HIV, including FSWs. However, significant gaps remain in HIV testing coverage in sub-Saharan Africa.^8^ Given the large burden of HIV among FSWs and the unique barriers to HIV prevention faced by this population, evidence of strategies that are specifically designed for this population is urgently needed.

Stigma and discrimination can affect access to HIV testing among FSWs.^9^
^10^ FSWs may be affected by multiple intersecting forms of stigma. Stigma is broadly defined as negative attitudes, relative powerlessness and loss of status related to a particular characteristic.^9^ Stigma can be experienced as enacted (explicit actions such as derogatory language, active discrimination or assault), perceived (the expectation of enacted stigma) or self-stigma (internalisation of stigma).^10^ For FSWs, stigma can be due to engagement in sex work itself, or from HIV stigma, particularly in contexts of high HIV burden, and can come from family or other community members, partners and healthcare providers. These experiences of stigma may be exacerbated by unequal power dynamics, poverty and financial reliance on sex work, and experiences of violence. Taken together, the multidimensionality of experiences of stigma and discrimination may greatly influence uptake of HIV testing. Interventions that mitigate stigma as a barrier to HIV testing may be especially powerful for FSWs.

Oral HIV self-testing (henceforth, HIVST) is an alternative to clinic or other healthcare provider testing (eg, home-based HIV testing and counselling) that may overcome some barriers to traditional HIV testing strategies for some populations.^11–14^ HIVST has been shown to be acceptable in a variety of populations globally,^11^ but very little data exist on the acceptability and feasibility of HIVST among FSWs.^13^ For FSWs in particular, HIVST may be a particularly good option as it offers privacy protection, efficiency and flexibility. FSWs are a vulnerable population regarding potential harms and threats to livelihood if others are to learn they are HIV positive. HIVST may offer an additional degree of privacy by allowing women to test in a place of their choosing. HIVST may be efficient for FSWs. Current recommendations indicate that FSWs should ideally test for HIV every 3 months. HIVST could reduce the burden of transport to clinics for traditional testing. Finally, HIVST is flexible. Existing clinics may not offer HIV testing services during hours which are feasible for FSWs, who often sleep during the day and work during the night. HIVST can overcome each of these limitations by allowing a woman to test at a time and a place that is convenient and acceptable to her.

A rapid oral HIVST has been approved in the USA, which uses fluid from the oral mucosa and is read in 20 min.^15^ The test, OraQuick (OraSure Technologies, Bethlehem, Pennsylvania, USA), has a sensitivity of 91.7% and a specificity of 99.9% among untrained users.^16^ All individuals who test positive with this test are encouraged to get a blood-based confirmatory test. Among men who have sex with men in Seattle, a randomised controlled trial demonstrated a significant increase in HIV testing coverage among individuals receiving HIVST.^17^ Although HIVST may be an acceptable alternative to regular HIV testing for FSWs, minimal evidence of the use of HIVST among FSWs exists.^18^ The acceptability, uptake, and effectiveness and safety of HIVST among FSWs remain largely unknown.

Here, we describe a cluster randomised controlled trial that addresses this critical gap in the HIVST evidence for FSWs. In the trial, we test two health service delivery approaches, a direct distribution system where an FSW participant is directly given an HIVST by a peer, and a fixed distribution system where the FSW participant collects the HIVST from a fixed point such as a pharmacy or health post. The trial seeks to determine the effectiveness and safety of these two HIVST delivery approaches, compared with standard of care, for improving HIV testing coverage and knowledge of HIV status.

## Methods/design

### Theory of change

The intervention tested in the Zambian Peer Educators for HIV Self-Testing (ZEST) study, as well as data collected throughout the course of the study, was guided a priori by a theory of change developed through mental models and deductive development.^19^ Briefly, we theorised that the distribution of HIV self-test kits via peer educators would lead to improved status knowledge by reducing barriers to HIV testing such as stigma hours of clinic operation. Enacted or perceived sex work stigma from healthcare providers and from the community may be addressed by HIVST, by allowing individuals to test for HIV in private without fear of being seen in the clinic and without fear of judgement from providers. This would lead to improved uptake of HIV testing, which would lead to improved knowledge of status and ultimately reduce time to linkage to care. However, it is also possible that a community-based intervention such as HIVST could be unsuccessful if individuals are concerned about others discovering their HIV status.

### Study design

This is a unmasked cluster randomised trial. Individuals are enrolled as members of a peer educator group, with a target enrolment of six FSWs per peer educator (with five allowed if there are recruitment difficulties). The peer educator–FSW group is randomised in a 1:1:1 fashion to one of the three study arms: (1) peer educator distribution of HIVST directly to participants (direct distribution), (2) peer educator distribution of a coupon valid for an HIVST at a fixed distribution point (fixed distribution) or (3) standard of care. Participants will be followed for 4 months from enrolment, with follow-up assessments at months 1 and 4 (figure 1).

**Figure 1 BMJOPEN2016014780F1:**
[figure not shown]
Flow diagram of study enrolment, randomisation and intervention arms. FSW, female sex worker; HIVST, HIV self-testing; STD, sexually transmitted disease; IPV, intimate partner violence.

### Specific aims

The specific aims of this trial are to: (1) establish the effectiveness of two different distribution approaches (direct and fixed distribution) for increasing HIV testing coverage among FSWs; (2) establish the effectiveness of the two distribution approaches on increasing HIV status knowledge among FSWs; (3) measure HIVST uptake by distribution approach and (4) measure linkage to care by the different approaches. Additionally, the trial will measure the impact of HIVST using the two distribution approaches on a number of important safety end points. The trial design will allow for a comparison of the two distribution approaches to each other as well as to standard HIV testing.

### Study oversight

An independent Scientific Oversight Committee (SOC) oversees the data collected as part of this study. The SOC contains members with expertise in HIV epidemiology, statistics, ethics and female sex work. The SOC reviews any reports of serious adverse events during the course of the trial, and will convene a meeting after approximately one-third of the participants have reached their 1-month visit. Owing to the short duration of the study, there are no formal statistical stopping rules.

### Setting

This study is taking place in three border and transit towns in Zambia: Chirundu, Livingstone and Kapiri (figure 2). Chirundu and Livingstone are located on the Zambia–Zimbabwe border, and are major transportation points for people and goods. Kapiri is north of the capital, Lusaka, and is a transit hub, with a large weigh station where many truckers stop for the night or longer. Study headquarters and coordination for the three sites is located in the capital, Lusaka.

**Figure 2 BMJOPEN2016014780F2:**
[figure not shown]
Map of study sites in Zambia. The black star indicates Lusaka, the site of study coordination and headquarters. The circles indicate locations of study sites, including Kapiri (blue), Chirundu (green) and Livingstone (red).

### Recruitment

Participants are recruited by peer educators. The peer educators are current or former FSWs themselves who were recruited by study staff and who have undergone a 2-day training in study procedures and HIVST. Peer educators, who are not considered as participants in this study, were recruited from current and former sex work organisations working in each of the study towns. Interested potential participants are referred to study staff after the peer educator describes the study to them. A research assistant then conducts a phone screening to determine whether or not the participant is eligible. Formal eligibility assessments are done in person at which point the research assistant and eligible individuals complete an informed consent procedure. Written informed consent is obtained from all participants.

### Inclusion and exclusion criteria

Complete inclusion and exclusion criteria are summarised in table 1. Participants must be women 18 years of age or older who self-report exchanging sex (including vaginal, anal and/or oral) for money or goods in the past month.

**Table 1 BMJOPEN2016014780TB1:** Study inclusion/exclusion criteria

Inclusion criteria	Exclusion criteria
▸ 18 years or older at enrolment	▸ <18 years at enrolment
▸ Reports exchanging sex (vaginal, oral and/or anal) for money or goods at least once in the past month	▸ Has not exchanged any form of sex in the past month
▸ Self-reported HIV negative and no recent HIV test (<3 months) OR HIV status unknown	Self-reported to be living with HIV Self-reported HIV negative but tested within the past 3 months
▸ Permanent residence in the study town of enrolment (Livingstone, Chirundu, Kapiri)	Planning to move out of the geographical area within 4 months Living in the PopART catchment area (Livingstone only)
▸ Willing to participate in peer education sessions and study assessments over a 4-month study period	▸ Meets inclusion criteria but does not wish to participate
	▸ Concurrently participating in another HIV prevention study

Individuals who are currently residing in the PopART study catchment area^20^ in Livingstone will be excluded from this study, in addition to any individual who reports concomitant enrolment in another HIV prevention study. The PopART study includes a household HIV testing programme, which would bias outcomes in this study if individuals were being regularly tested as part of another HIV prevention study.

### Randomisation

Peer educator groups (the 5–6 women recruited by a particular peer educator and enrolled in the study) are randomised as a unit. Group randomisation occurs after all members of the group have been enrolled in the study and completed their baseline questionnaire. Groups are randomised to one of the three study arms using a computer-generated randomisation list in random blocks of 3, 6 and 9 and stratified by study site (Livingstone, Chirundu and Kapiri). Randomised study arm assignments are placed in an opaque envelope, and once all participants in a peer educator group have been enrolled, the research assistant obtains the envelope from the research coordinator or the site coordinator and opens the envelope with the peer educator.

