### Study procedures

An overview of the study procedures and activities is summarised in table 2 and figure 3.

**Table 2 BMJOPEN2016014780TB2:** Outline of study visits

Study time point	Visit by	Activities
Recruitment	Peer educator	▸ Peer educator discusses study with potentially eligible participant and refers them to study staff
Enrolment	Research assistant	Assessment of eligibility Informed consent (if eligible) Baseline quantitative survey Baseline qualitative survey (∼5%)
Randomisation	Research assistant	▸ Randomisation of peer educator and their cohort of participants once all group members are enrolled
Intervention visit 1 (week 0)	Peer educator	Group-based intervention HIV prevention counselling and distribution of condoms Training on HIV self-test use (in HIVST arms) Distribution of HIV self-tests or coupons (in HIVST arms)
Intervention visit 2 (weeks 2–3)	Peer educator	Screening for adverse events Discussion of any difficulty with HIV self-test use (in HIVST arms) Referral to care and standard HIV testing Distribution of condoms
One-month visit (weeks 4–5)	Research assistant	One-month quantitative survey One-month qualitative survey (∼5%) Screening for adverse events
Intervention visit 3 (weeks 6–7)	Peer educator	Screening for adverse events Discussion of any difficulty with HIV self-test use (in HIVST arms) Referral to care and standard HIV testing Distribution of condoms
Intervention visit 4 (weeks 10–12)	Peer educator	Screening for adverse events Discussion of any difficulty with HIV self-test use (in HIVST arms) Referral to care and standard HIV testing Distribution of condoms Distribution of second HIV self-test or coupon (in HIVST arms)
Four-month visit (weeks 16–18)	Research assistant	Four-month quantitative survey Four-month qualitative survey (∼5%) Screening for adverse events HIV status assessment

HIVST, HIV self-testing.

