#### Peer educator visits

In all study arms, peer educators will meet with participants at least four times (approximately monthly) over the course of the study. The first peer educator intervention visit (intervention visit 1) will be a group-based visit, and includes simple HIV prevention information, information on where to go for HIV testing and condom provision. The initial group-based intervention is organised by the peer educator with assistance from the research assistant, and occurs in a private location of mutual convenience for the group members (such as a study office, or near a work place). In the HIVST arms, peer educators will provide a brief overview of how to use the self-test kits, whom to contact if participants have problems or concerns, and the importance of as well as how to obtain additional care, including confirmatory testing and linkage to care. Follow-up visits (intervention visits 2–4) with peer educators comprise brief one-on-one check-in visits, during which peer educators will distribute condoms, discuss any issues participants have with the HIVST kits or other elements of the study, and screen for adverse events including intimate partner violence. Between visits, peer educators will be available should participants need help with any issue relating to safe sex, HIV, violence or any other elements of the study. Peer educators do not specifically discuss HIV status with any participant unless the participant seeks out the peer educator for advice. Participants are given alternatives should they need help with HIVST or another element of the study but do not want to disclose their HIV status to the peer educator. In particular, participants in all study arms also have access to an anonymous 24-hour hotline provided via the study. Participants will be instructed by the research assistant that they can call the 24-hour hotline at any time if they have difficulty with using the HIV self-test kit, need counselling related to HIV testing or gender-based violence, or need any other form of assistance over the duration of the study.

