### Data collection

#### Baseline survey: enrolment

At the enrolment visit, all participants complete a quantitative questionnaire administered by a research assistant. Quantitative data are collected directly on a tablet. All assessments are conducted in a private room at a time and location that is convenient to the participant. The baseline survey covers broad topics including demographics and household composition, sex work and professional history, reproductive health and contraception, sexual behaviours, HIV testing history, attitudes towards HIVST, access to healthcare, and measures of substance use,^21^ depression,^22^ social support, self-efficacy,^23^ and empowerment.^24^

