#### One-month and 4-month visits

Follow-up surveys will be conducted at the 1-month and 4-month visits from intervention visit 1 (see table 2). As with the baseline survey, all quantitative data will be collected via a tablet, and qualitative data (4-month visit only) are collected via an audio recorder. Participants in all arms of the study will be asked about their recent HIV testing history, sexual behaviours, access to healthcare and linkage to care. In the HIVST arms of the study, participants will additionally be asked about their experiences with the HIVST kit, including if they used it and details about their experience using the test, as well as their experience with the peer educator. Participants in all arms are asked again at 1 and 4 months about HIVST acceptability and perceived likelihood of using such tests in the future.

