### End point measurement

Study effectiveness and safety end points are summarised in table 3. The primary effectiveness end point for the study is the proportion of participants who tested in the previous month as assessed at the 1-month follow-up visit. Secondary effectiveness end points include testing at 4 months, awareness of HIV status, HIVST kit use (restricted to the HIVST arms), linkage to care and adverse events. Safety end points include intimate partner violence and mental health.

**Table 3 BMJOPEN2016014780TB3:** Summary of study end points

End point	Operationalisation
*Primary effectiveness end point*	
Tested for HIV in the past month	Recent HIV testing measured by asking participants when they last tested and where (in all arms of the study)
*Secondary effectiveness end points*	
Use of HIV self-test	Measured by buying back unused HIV self-tests at the 4-month visit
Awareness of HIV status	Measured using a three-step approach: (1) asking participants if they know what their status is; (2) offering participants a small financial gift if they can correctly tell the interviewer what their HIV status is; 3) confirming HIV status with a rapid test
Linkage to care and confirmatory testing	Measured in two ways: (1) during follow-up visits, asking participants if they received confirmatory testing and linked to care; and (2) collection of referral cards linking individual HIV self-tests to individuals via a unique identification number
Sexual behaviours	Measured via CAPI, including number of sexual behaviours, event-level sexual behaviour data, and condom use with primary and casual partners
*Safety end points*	
Misuse of HIV self-tests	Including difficulty conducting the test (ie, mistakes in taking the test, incorrect use of components of the test), difficulty reading the test Identified through interview and ongoing consultation with peer educators
Intimate partner violence	Measured through surveillance and interviews by research assistants Any intimate partner violence (including verbal, physical or sexual) will be documented and reported

CAPI, computer-assisted personal interview.

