#### HIVST kit use

Actual use of the HIVST kit may also be subject to social desirability bias. Participants may want to report that they used the HIVST kit when they did not for many reasons, including a desire to please the researchers, a sense of obligation or misperception about what it means to use the test.^25^ As an attempt to reduce bias in ascertainment of actual use of the HIVST kits, research assistants will ask participants to buy back any unused HIVST kits at the end of the study with the justification that the study has now reached completion. Participants will be offered ∼US$1 in exchange for any unused test kits in their original packaging. Prior to this offer, participants are not told that researchers will buy back tests at the end of the study (this information is also not included in the informed consent). To avoid gossip among study participants, the first buy-back will not happen until at least 1 month after the last test kit has been distributed (with the assumption that all participants would have used the test kit at that point if they were planning to).

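### Nothing keeps a research assistant who knows a group's arm from taking that group's self-reported primary end point, which leaves the contrast open to interviewer bias of unknown size

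*Protocol article*

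**What the plan says.** The Study design section of the protocol article is plain about masking: "This is a unmasked cluster randomised trial". The research assistant role then appears at four points.

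- **Enrolment.** Under Baseline survey, "all participants complete a quantitative questionnaire administered by a research assistant".
- **Allocation.** Under Randomisation, after the last woman in the group has enrolled, "the research assistant obtains the envelope from the research coordinator or the site coordinator and opens the envelope with the peer educator".
- **First session.** Under Peer educator visits, "The initial group-based intervention is organised by the peer educator with assistance from the research assistant". Table 2 places self-test training and the handing out of kits or coupons at this session and lists it as a peer educator visit.
- **Outcome.** Table 2 lists the 1-month and 4-month surveys as research assistant visits.

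The End point measurement section sets the primary end point as testing in the previous month, taken at the 1-month visit. Table 3 gives its measurement as "Recent HIV testing measured by asking participants when they last tested and where (in all arms of the study". The Recent HIV testing section confirms that this is self-report.

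On bias, the HIVST kit use section says: "Participants may want to report that they used the HIVST kit when they did not for many reasons, including a desire to please the researchers". The responses to that are the buy-back of unused kits and, for status knowledge, a three-step assessment with a perceived incentive and a voluntary rapid test. Both take place at the 4-month visit.

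**The concern.** Participants and peer educators cannot be masked in this trial. The interviewer's knowledge of the arm is the one part of the chain that can be limited at little cost. The plan gives the opening of the envelope to the role that later asks the primary question, and sets no rule to separate the two tasks.

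The article itself supplies the mechanism: obligation, and the wish to please the study team. That pressure is likely to be stronger in the HIVST arms, because only those women received a kit or coupon from the study that they would have to admit leaving unused. An interviewer who knows the arm, or who was seen to help set up the session, can add to it through tone, probing or mere presence. No objective check covers the 1-month answer. If the interviewer adds to over-reporting more in the HIVST arms than in control, the risk ratio and the type I error of the primary comparison both rise.

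**Working it through.** **Inputs (Sample size considerations).** 300 women and 50 clusters per arm, 20% loss, intracluster correlation 0.03, alpha 0.05 (taken as two-sided; the article does not say), 50% testing in control, risk ratio 1.30.

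**Step 1: reproduce the stated power.**
- Evaluable per arm: 300 × 0.80 = 240, or 240/50 = 4.8 per cluster.
- Design effect: 1 + (4.8 − 1) × 0.03 = 1.114.
- Effective n per arm: 240/1.114 = 215.4.
- Power for 50% against 65%: 88.6% with pooled variance and 89.0% with unpooled variance.

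The article states 89%, so the same set-up can carry the illustration.

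**Step 2: false rejection under differential over-reporting.** Suppose there is no true effect (50% in both arms). A fraction f of HIVST-arm non-testers report a test and no control non-testers do. The value of f is an assumption; the article gives none.
- Reported rate in the HIVST arm: p2 = 0.50 + 0.50f. Observed risk ratio: p2/0.50 = 1 + f.
- With p̄ = (0.50 + p2)/2: se0 = √[2p̄(1 − p̄)/215.4] and se1 = √[(0.25 + p2(1 − p2))/215.4].
- Chance of p < 0.05: 1 − Φ[(1.96·se0 − (p2 − 0.50))/se1], plus the small lower tail.

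For f = 10%: p2 = 0.55, se0 = 0.0481 and se1 = 0.0481. The upper tail is 17.8% and the lower tail 0.1%, which gives 18.0%.

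| f | Reported rate, HIVST arm | Observed RR | False rejection |
|---|---|---|---|
| 0 | 50% | 1.00 | 5% |
| 5% | 52.5% | 1.05 | 8% |
| 10% | 55% | 1.10 | 18% |
| 20% | 60% | 1.20 | 55% |
| 30% | 65% | 1.30 | 89% |

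**Step 3: what the table does and does not measure.** It shows total differential over-reporting, whatever its source. If control non-testers over-report at rate g, the observed risk ratio becomes (1 + f)/(1 + g). For f = 10% and g = 5% this is 1.10/1.05 = 1.05. For f = g it is 1.00, with no inflation.

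Only the interviewer's share of f can be removed by separating roles, and that share is unknown. With f = 10% and g = 0, the table gives the range: if the interviewer accounts for none of it, 18% remains; if for half, f falls to 5% and 8% remains; if for all, 5% remains.

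**The case against.** The case against is substantial, and several parts of it stand.

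- **Delivery is already a peer educator task.** A reader might infer that the interviewer trains women or hands out kits. The article does not support that. Table 2 and the arm descriptions give training and distribution to peer educators, and the assistant helps to organise the session. Attendance is not stated either.
- **A role is not a person.** A reader might infer that one individual enrols, opens the envelope and interviews the same group. The article never says so, and interviewer rosters are a detail that an article may leave to the full protocol. The point here does not rest on that missing detail. It rests on what is stated: the interviewing role is the one assigned to open the allocation.
- **The pressure is not purely one-sided.** Control women also have peer educator visits, are told where to test and, at intervention visit 2, are referred for standard testing before the 1-month survey. They may over-report too. This narrows the difference and need not cancel it.
- **Question order is not shown to be wrong.** The article says "In the HIVST arms of the study, participants will additionally be asked about their experiences with the HIVST kit". That does not place the kit questions ahead of the testing question.
- **Some checks exist.** Scanned coupons would expose a self-test claimed in the fixed arm without kit collection, and the 4-month checks bear on plausibility. So it goes too far to say that a positive result could not be told apart from courtesy bias. But a coupon shows collection and not testing, the direct arm has no such record, and neither 4-month check verifies the 1-month answer.

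The Strengths and limitations list openly declares self-report and social desirability as limitations. It does not mention the interviewer's knowledge of the arm.

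**Conclusion.** The concern holds in a limited form. The plan puts opening the allocation, helping to organise the first session and taking the self-reported primary end point in one role, and has no rule to keep an assistant who knows a group's arm from interviewing that group. The stated anti-bias measures protect only secondary end points. This leaves room for an interviewer contribution to differential over-reporting. Its probable direction favours the HIVST arms, which is an inference from the article's own remarks on kit use.

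The size of that contribution cannot be derived from the article. The 18% figure assumes 10% false reporting among HIVST-arm non-testers, none in control and no true effect. It describes all courtesy bias together and should not be read as the effect of the interviewer. The stated power is unaffected. This is a worthwhile, inexpensive improvement; it does not invalidate the design.

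**What to change.** 1. **Interview assignment.** With existing staff, where a site has more than one research assistant, give each group's 1-month and 4-month interviews to one who neither opened that group's envelope nor helped with its first session and is not told the arm.
2. **Sites with a single assistant.** The article does not give staffing per site. Where there is only one, the site or research coordinator, who already holds the envelopes, can open them with the peer educator. The interviewer should then be kept out of the first session as far as possible.
3. **Tablet form.** In every arm, ask the items on when and where the woman last tested, and lock the answers, before any arm-specific kit questions open. If the form already runs in this order, only the lock is new.

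If the full protocol already separates these tasks, a sentence saying so settles the first two items.

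The cost is a little scheduling work, a small change to the form and some loss of rapport. The interviewer may learn the arm from the answer on where, but only after the answer on timing has been entered. Participants still know their arm, so courtesy bias is reduced and not removed.
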